## Objectives and endpoints

Our primary objective is to assess the correlation of FDG-PET activity with changes in HIV RNA in lymphoid tissues before and after ATI. Secondary objectives will evaluate correlation of FDG-PET with HIV RNA in other compartments, as well as characterize changes in both DNA and RNA. Objectives and endpoints are summarized below in Table 1.

**Table 1 T1:** Study objectives and endpoints.

**Objectives**	**Endpoints**	**Justification for endpoints**
**Primary**		
To evaluate if changes in glucose metabolism (as measured by FDG-PET SUV) correlate with changes in levels of HIV RNA in lymphoid tissue before and after ATI	Proportion of participants who have a 3-fold increase in HIV RNA levels in tissue sites identified by imaging as having increased SUV on FDG-PET as defined below	There are limited data on sensitivity of FDG-PET to detect HIV-infected cell populations during ATI. We will determine utility of this approach for investigating HIV persistence in people living with HIV

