#### Baseline/First imaging visit

At baseline, blood will be drawn *via* venipuncture for clinical and research evaluations, and participants will undergo whole body FDG PET/CT. Within the next 5 days, PBMCs will be collected by leukapheresis, and lymphoid tissue biopsies will be taken on the basis of imaging results. Approximately 2–5 biopsies will be performed after each PET scan. PET-avid (“hot”) and non-avid (“cold”) areas will be sampled. Lymph node biopsies will be guided by the combination of modalities most appropriate for each biopsy, which may include CT, ultrasound, and anatomic landmarks. Approximately 3 needle passes are typically performed, with the exact number guided by cytology feedback, intra-procedural factors, maintenance of low-risk, and size of target. Hot and cold nodes will be biopsied based on accessibility, with consideration for prior biopsies and consistency in biopsy site across participants. Optional sample collections are bone marrow biopsy, CSF *via* LP, and vaginal fluid or semen samples (which may be collected at home for the participant's convenience). Research evaluations on the samples are described in Table 2.

**Table 2 T2:** Biospecimen evaluations.

**Samples to be collected**	**Collection method**	**Study requirements**	**Analyses planned for samples (assuming sufficient material obtained)**
Peripheral whole blood	Venicpuncture	Required	• Human leukocyte antigen (HLA) testing • Collection of PBMCs • Characterization of HIV populations • Sequencing of HIV-1, including ARV resistance testing • Inflammatory markers/cytokine profiling • Soluble markers of immune response • ARV drug levels • Interferon gene variant analysis • Storage for future research
Peripheral leukocytes	Leukapharesis	Required	• T-cell repertoire • Characterization of HIV populations • Sequencing of HIV-1, including ARV resistance testing
Cerebrospinal fluid	Lumbar puncture	Optional	• Albumin • Quantitative amino acids • Glucose • IgG • Total protein • Cell count and differential • Blood • HIV quantitative PCR • HIV sequencing • Cytokine analysis • Storage for future research

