Initial data analysis will entail measurement of total HIV RNA by polymerase chain reaction (PCR) from lymph node biopsy specimens. Comparisons will be made between the ATI and continued-ART groups, as well as within each randomization group across time points. This analysis will be used to (1) determine if ATI participants vs. controls could be identified *via* PET/CT, and (2) determine if viral RNA in lymph nodes increased over the course of ATI. Based on the results of the analysis of this group, we may need to adjust the timing of the first PET/CT with biopsy after ATI; this change will be done through a protocol amendment. If it is determined after the first 12 participants that the timing of the first PET/CT with biopsy should be adjusted, according to criteria outlined under “PET/CT and Biopsy Timing Justification” (0–1 ATI participants has >3 fold increase RNA in a biopsy site OR none of the 6 ATI participants are correctly classified), then the study would be repeated with new participants and a modified schedule with the 2nd imaging and biopsy assessment moved to 14–17 days post-ATI. If all 6 have 3 fold tissue RNA increase, we will move the imaging and biopsy to 3–6 days post-ATI. The study would be repeated with the same number of participants. Data analysis would be repeated using the same criteria. The study may be repeated more than once, if needed. Additional repetitions would shift the imaging and biopsy by increments of 4 days.

Study visits will typically be done as outpatients, but participants may be admitted as inpatients at the discretion of the investigators.

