### PET/CT and biopsy timing justification

The timing of our interventions is based on current understanding of HIV rebound and imaging capability. If we do not find that analysis of FDG-PET is sufficiently sensitive to detect differences in metabolic activity, or we do not find increases in HIV RNA in tissues, the timing of imaging is likely too early and we will amend the protocol to extend the timing of the biopsy relative to the ATI start.

Conversely, if lymph node biopsies from all participants have a significant increase in HIV RNA after the first assessment, then the samples were likely collected too late and do not reflect the early stages of viral rebound. In this case, the study would be repeated with the first post-ATI assessment moved earlier. In some instances where consistency in biopsy site is not possible, different lymph nodes, preferably in the same region, will be biopsied across time points. Evidence suggests compartmentalization between different lymph nodes in the same individual does not occur (70).

After completing the analysis to examine data from the first 12 patients, the first PET/CT with biopsy will be moved from days 10 ± 3 post-ATI based on the following criteria:

a. Move later, to days 14 to 17 post-ATI

i). If 0/6 or 1/6 ATI patients have 3-fold increase in viral RNAii). If 0/6 ATI patients are recognized on PET/CT

b. Move earlier, to days 3 to 6 post-ATI

i). If 6/6 ATI patients have 3-fold increase in viral RNA

A 3-fold increase in HIV RNA is being used as the threshold because it represents an increase that is significantly different by single-copy assay.

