## Discussion

HIV is controlled but not cured by combination antiretroviral therapy, and the mechanisms of HIV persistence remain poorly characterized. ATI studies have been useful in investigating the events in HIV rebound (71–77); many ATI studies analyze HIV present in plasma or in peripheral blood mononuclear cells. Most replication takes place in tissues, however, and HIV reactivation in tissues during ATI has not been well-studied. This protocol will allow us to explore utility of PET for identification of areas of high FDG uptake indictive of increased metabolic activity. By biopsying both FDG hot and FDG cold areas, we will be able to characterize these regions and investigate HIV replication during treatment interruption. One hypothesis is that PET SUV correlates with HIV viral RNA in biopsy of those regions and that lymph nodes with high SUV have higher viral RNA compared with areas with low SUV within a patient. If this is true, PET may be useful for identification of HIV infected cell populations, as well as monitoring response to cure strategies.

A randomized design was selected for this study to account for natural variation that might be seen in FDG uptake over time and to test the hypothesis that ATI engenders changes in FDG uptake not seen in patients who continue ART. Neither of these considerations could have been addressed without inclusion of the control ART continuation group. The possibility of doing only the ATI group, with each participant's baseline scan serving as their own control, was explored. Natural longitudinal variation in FDG uptake could, however, confound this approach. As Pfaehler and coworkers have reported, FDG PET uptake may be subject to variation from a number of potential sources (78, 79). Randomization to ATI vs. continuation of ART was necessary to optimize the balance of additional known and unknown confounders. The data generated, using rigorous uptake quantification, will also serve as an assessment of natural variation in FDG uptake over time, which will have general utility for FDG uptake studies.

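### The primary endpoint counts HIV RNA rises only in sites with increased SUV, so it cannot show that SUV change tracks RNA change

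*Protocol article*

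**What the plan says.** The section Objectives and endpoints gives the primary objective as to "assess the correlation of FDG-PET activity with changes in HIV RNA in lymphoid tissues before and after ATI". Table 1 repeats it: changes in SUV are to be examined for whether they "correlate with changes in levels of HIV RNA in lymphoid tissue before and after ATI". The endpoint in the same row is "Proportion of participants who have a 3-fold increase in HIV RNA levels in tissue sites identified by imaging as having increased SUV on FDG-PET", with the definition of increased SUV left to later text.

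Elsewhere in the protocol article:

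- **Sampling.** Under Baseline/First imaging visit, PET-avid and non-avid "areas will be sampled", and "Approximately 2–5 biopsies will be performed after each PET scan". The split between hot and cold sites is not given.
- **Hot versus cold.** The section comparing PET hot and cold biopsy samples plans a within-participant rank comparison with a permutation test. It is limited to ATI participants with hot spots, and the analyte is HIV DNA.
- **RNA comparisons.** Under Resume ART phase or continue ART phase, total biopsy RNA is compared between arms and across time points within arms. SUV status is not part of that comparison.
- **Timing rule.** One condition for moving the post-ATI imaging later is "0–1 ATI participants has >3 fold increase RNA in a biopsy site"; the other is that the blinded reader recognises none of the six ATI participants. If all six have a 3-fold rise, imaging moves earlier. The 3-fold cut is used because "it represents an increase that is significantly different by single-copy assay".

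**The concern.** A correlation needs variation in both quantities. The endpoint holds one of them fixed: it looks only where SUV has increased and asks how often RNA rose there. Nothing in it depends on RNA in nodes where SUV did not increase.

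The Discussion states the hypothesis as a contrast within a patient: nodes with high SUV carry more viral RNA than areas with low SUV. The Introduction leaves open whether uptake marks replication or only immune activation. If RNA rises throughout lymphoid tissue after ATI, the endpoint could be high although PET adds nothing about where. The trial would then report a favourable primary result that does not answer its primary question, after invasive sampling that had collected the cold-site tissue needed to answer it.

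**Working it through.** **The plan's own figures.** The article gives no expected value or power for the primary endpoint. Its only sample-size figures concern the blinded reader's classification of arm. They reproduce as one-tailed Fisher tests with one error in each arm:

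- 6 v 6: (36 + 1)/924 = 0.040
- 5 v 5: (25 + 1)/252 = 0.103

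They say nothing about SUV against RNA.

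**Same endpoint, different associations.** Take one hot and one cold site per participant, with 3-fold-rise rates a (hot) and c (cold). The endpoint equals a. The association between SUV status and RNA rise is phi = (a − c)/√[(a + c)(2 − a − c)]. With a = 0.80 (assumed):

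| Cold-site rate c | Endpoint | phi |
|---|---|---|
| 0% | 80% | 0.82 |
| 20% | 80% | 0.60 |
| 80% | 80% | 0.00 |
| 95% | 80% | −0.23 |

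**How high it can read when PET is uninformative.** Let q be the chance of a 3-fold rise at any node and h the number of hot sites biopsied. Assume that nodes are independent and that one qualifying hot site is enough. The documents give neither q nor h. The expected endpoint is 1 − (1 − q)^h:

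| q | h = 1 | h = 2 | h = 3 |
|---|---|---|---|
| 0.1 | 10% | 19% | 27% |
| 0.3 | 30% | 51% | 66% |
| 0.5 | 50% | 75% | 88% |
| 0.8 | 80% | 96% | 99% |

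At q = 0.8, the binomial chance that at least 5 of 6 ATI participants meet the endpoint is 66% with h = 1 and 98% with h = 2, with no association at all.

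**Response to the correlation itself.** This was simulated with four sites per participant, the two with the largest SUV change counted as hot, and an SD of RNA change of 0.5 log10 (all assumed).

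| SUV–RNA correlation | Hot / cold proportion, mean rise 1.0 log10 | Hot / cold proportion, mean rise 0.3 log10 |
|---|---|---|
| −0.5 | 95% / 99% | 41% / 73% |
| 0 | 98% / 98% | 59% / 59% |
| 0.5 | 99% / 95% | 74% / 41% |
| 0.8 | 99.8% / 92% | 80% / 27% |

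With a large mean rise the hot-site proportion hardly moves. With a small mean rise it does move, but its level depends on the unknown mean rise as well as on the correlation. The cold-site figure shows the direction in both settings.

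**Do other described analyses supply the contrast?**

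- The hot/cold permutation test uses HIV DNA values, not RNA change. The Introduction reports that on ART viral RNA falls a median of 17,000-fold and cell-associated DNA only 10- to 30-fold, so the two analytes are not interchangeable.
- The RNA comparisons are by arm and time.
- The Bayesian estimate of a productive hot spot is described for hot spots only.
- The secondary correlation endpoint in Table 1 relates SUV to sequencing characteristics, not to RNA level.

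None compares RNA change between increased-SUV and other sites.

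**Can the contrast be tested?** With one hot-minus-cold difference per participant, the smallest one-sided sign-flip p is 1/2^6 = 1/64 = 0.016 with six evaluable participants and 1/2^4 = 1/16 = 0.0625 with four.

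**The case against.** Several counter-arguments have force.

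- **The trial does have comparators.** A reader might infer that it lacks cold-site data or makes no use of its controls. That is not so. Cold areas are biopsied, a hot/cold test is planned, biopsy RNA is compared between arms, and the blinded reader's task of telling ATI from control scans is one limb of the timing rule. Only the RNA limb counts ATI participants alone.
- **The controls serve another purpose.** The Discussion justifies them by variation in uptake: "Natural longitudinal variation in FDG uptake could, however, confound this approach". Participants who stay on ART cannot show whether RNA rises equally in hot and cold nodes after ATI. The endpoint names no arm and could be tabulated in both, but that would speak to the effect of ATI, not to whether SUV tracks RNA across sites.
- **A 6/6 result would not simply stand as success.** The plan reads it as sampling too late and repeats the study earlier. That covers 6/6 only; 5/6 does not trigger it.
- **Details may lie in Supplementary material S1**, which is not shown. It may refine what counts as increased SUV. An endpoint confined to such sites would still omit the cold ones.
- **A stronger claim about noise is not supported.** One might infer that biopsy-to-biopsy variation alone would satisfy the RNA limb of the timing rule. With three sites and no true change, at least 2 of 6 participants would be flagged in 18%, 67% or 95% of cohorts for an assumed between-biopsy SD of 0.2, 0.3 or 0.5 log10. The arithmetic is sound, but the documents give no SD and the answer follows almost entirely from the one chosen. It also concerns the any-site timing rule, not the primary endpoint.

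What remains is that no described analysis contrasts RNA change by SUV status.

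**Conclusion.** The primary objective and primary endpoint do not match. This follows from the text and needs no assumption: a proportion taken only in increased-SUV sites is unchanged by anything that happens in cold sites, so it cannot estimate or test the stated correlation.

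How misleading it could be does rest on assumptions. With PET uninformative, the endpoint runs from 10% (q = 0.1, one hot site) to 99% (q = 0.8, three hot sites). It is high only if RNA rises widely after ATI. The protocol's own rule for 6/6 shows that a rise in every ATI participant is foreseen, but the documents give no rate per node.

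The finding does not extend to saying that the controls are unused or that the timing rule is driven by noise.

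**What to change.** 1. Pair the primary endpoint with a within-participant contrast in ATI participants: log10 tissue RNA change from baseline to the second scan in increased-SUV sites, minus that in cold sites.
2. Test it by the permutation procedure already planned for hot and cold samples, applied to RNA as well as DNA.
3. Report the 3-fold proportion for cold sites beside that for hot sites, with the number of sites of each kind per participant.
4. State how a baseline value is assigned when the same node cannot be re-biopsied. The current endpoint already needs this for hot sites; the contrast needs it for cold sites too.
5. For the RNA limb of the timing rule, report the control arm's any-site 3-fold rate beside the ATI count as a description of biopsy-to-biopsy variation. It should not be a decision threshold, because the intervals are unmatched: 12–16 weeks after baseline in controls against days 7–13 of ATI.

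**Cost.** The change needs endpoint wording and a modest extension of a planned analysis, with no new type of biopsy. The result may look less favourable than a one-group proportion. Participants without hot spots do not contribute, and with few evaluable participants the attainable p is limited: with four, the sign-flip test cannot fall below 0.05 one-sided. The estimated contrast and its participant-level values should therefore carry the interpretation.

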**Secondary**		
1. Characterize HIV populations (sequences) in sampled tissues, PBMCs, and plasma prior to and following ATI, and after treatment resumption 2. Assess relationship between changes in PET SUV and genetic characteristics (e.g., diversity, phylogenetics, and clonality) of HIV populations prior to, during, and after ATI 3. Assess relationship between changes in soluble and cellular immune parameters and imaging findings during viral rebound 4. Estimate replication competence of HIV variants from different anatomic compartments (sample tissues, PBMCs, plasma, semen, vaginal secretions, and CSF) 5. Compare kinetics of viral rebound after ATI with changes in immune activation markers	1. Levels of HIV DNA and integration site analysis to assess clonal distribution at different biopsy sites, semen, vaginal fluid, and PBMCs 2. Correlation between regional and overall change in PET SUV with HIV DNA and RNA sequencing characteristics pre-ATI to post-ATI 3. Cytokine and T-cell profiles during suppression and after ATI criteria for treatment resumption are met 4. HIV RNA and DNA sequence analyses for genetic studies and potential for replication competence 5. Correlation of HIV RNA levels and cytokine and T-cell profiles	HIV infection and viral replication are complex micro- and macro-level processes. Impact of ATI must be characterized at each of these levels for meaningful understanding of HIV persistence, and also to serve as a comparison point for future studies on this topic
**Tertiary/Exploratory**		
1. Evaluate interaction of host characteristics, HIV population characteristics, and immune profiles 2. Investigate HIV reactivation in other anatomic locations (CSF, semen, or vaginal secretions) in individuals who elect to undergo optional LP, or semen or vaginal secretion collection 3. Evaluate the relationship between FDG-PET SUV and immunologic activity 4. Investigate impact of ATI-associated changes in ART levels with changes in viral and immunologic characteristics	1. Correlations between HIV population markers, lymphocyte phenotype parameters, and participant characteristics 2. Comparative analysis of HIV DNA and RNA, levels of inflammatory markers, cytokine profiles, and antibody levels at different sites 3. Correlation between regional and overall change in PET SUV with changes in cytokine and T-cell profiles pre-ATI and post-ATI 4. Correlations of viral population changes, HIV DNA levels, HIV RNA levels, and immune markers with drug levels	Understanding the interaction between HIV populations and host characteristics is essential for devising eradication and cure strategies. Knowledge of adequacy of lymph node biopsy for virus characteristics and local immunologic milleu will inform future study design

## Methods and analysis

### Study design

This is a single-site randomized trial of the effects of ATI in six adult participants with HIV who are virally suppressed compared to six adult participants with HIV who are virally suppressed and who do not undergo ATI. Participants will be randomized 1:1 to either ATI or to continue their ART. Neither the participants nor the study team will be blinded, except for an imaging reader and biopsy reader, as described below. The study schema is shown in Figure 1. The schedule of events for participants randomized to ATI or to continue ART are shown in Supplementary Tables S2, S3.

**Figure 1 F1:**
[figure not shown]
Study schema. ART, antiretroviral therapy; ATI, analytic treatment interruption; VL, viral load. Depicts the overall schema for participant randomization and study procedures. Participants will be randomized 1:1 to continue ART or undergo ATI. ATI participants will undergo a total of three PET/CTs with biopsy, while those who continue ART will receive two PET/CTs with biopsy.

#### Screening

Up to 50 individuals will be screened in order to identify 12 individuals who will be enrolled onto the study. Inclusion and exclusion criteria are described below. Those who are determined eligible will return for a baseline/first imaging visit.

#### Baseline/First imaging visit

At baseline, blood will be drawn *via* venipuncture for clinical and research evaluations, and participants will undergo whole body FDG PET/CT. Within the next 5 days, PBMCs will be collected by leukapheresis, and lymphoid tissue biopsies will be taken on the basis of imaging results. Approximately 2–5 biopsies will be performed after each PET scan. PET-avid (“hot”) and non-avid (“cold”) areas will be sampled. Lymph node biopsies will be guided by the combination of modalities most appropriate for each biopsy, which may include CT, ultrasound, and anatomic landmarks. Approximately 3 needle passes are typically performed, with the exact number guided by cytology feedback, intra-procedural factors, maintenance of low-risk, and size of target. Hot and cold nodes will be biopsied based on accessibility, with consideration for prior biopsies and consistency in biopsy site across participants. Optional sample collections are bone marrow biopsy, CSF *via* LP, and vaginal fluid or semen samples (which may be collected at home for the participant's convenience). Research evaluations on the samples are described in Table 2.

**Table 2 T2:** Biospecimen evaluations.

**Samples to be collected**	**Collection method**	**Study requirements**	**Analyses planned for samples (assuming sufficient material obtained)**
Peripheral whole blood	Venicpuncture	Required	• Human leukocyte antigen (HLA) testing • Collection of PBMCs • Characterization of HIV populations • Sequencing of HIV-1, including ARV resistance testing • Inflammatory markers/cytokine profiling • Soluble markers of immune response • ARV drug levels • Interferon gene variant analysis • Storage for future research
Peripheral leukocytes	Leukapharesis	Required	• T-cell repertoire • Characterization of HIV populations • Sequencing of HIV-1, including ARV resistance testing
Cerebrospinal fluid	Lumbar puncture	Optional	• Albumin • Quantitative amino acids • Glucose • IgG • Total protein • Cell count and differential • Blood • HIV quantitative PCR • HIV sequencing • Cytokine analysis • Storage for future research
Lymph node tissue and bone marrow	Needle biopsy for lymph nodes, biopsy and aspirate for bone marrow	Lymph node biopsy is required, bone marrow biopsy is optional	• *In situ* hybridization, including RNAscope and DNAscope • HIV-1 viral load. HIV RNA levels will be normalized to total number of CD4 cells, quantified using CCR5 • Cell populations, flow cytometry • Immunohistochemistry • Cytokine analysis • Interferon sensitivity of replication-competent HIV recovered • Soluble markers of immune response • ARV drug levels • Genetic testing, including HLA typing • Storage for future research
Semen/vaginal fluid	Patient self-collection	Optional	• HIV RNA and DNA levels • Storage for future research

